### Sample Size Calculation

No precise data are available on the prevalence of SARS-CoV-2 infection among pregnant women in Brazil, but international reports have estimated that up to 15.3% of all pregnancies have been exposed to the virus [38]. Recent data have indicated a birth rate of 44,195 newborns per year in the Federal District [39]. Thus, after considering an “infinite” population (>20,000 pregnant women), assuming a 15% prevalence of SARS-CoV-2–exposed pregnancies, and accounting for a confidence level of 95% and a margin of error of 5%, the minimum sample size for a random sample of SARS-CoV-2–exposed women would be 195. This calculation expectedly yielded a similar number for a random sample of SARS-CoV-2–exposed children. If we set the expected dropout rate for the BORN substudy to 20%, the required number of SARS-CoV-2–exposed mothers (those giving birth to the BORN participants) would increase to 234.

Our sampling approach however is not truly random; it is based on convenience, as eligible subjects will present to the recruitment centers. The aforementioned calculations only serve as a reference for avoiding the overestimation of the inclusion of participants. Given the limited amount of available knowledge regarding the effects of SARS-CoV-2 infection on pregnancy and child development, which resulted in the eminently exploratory character of our study, we adopted an “as much as feasible, but no more than reasonable” approach for defining the sample size.

We set an a priori number of 300 SARS-CoV-2–exposed women for the PREGNANT phase. This will result in the inclusion of the expected 300 SARS-CoV-2–exposed children in the BORN phase. The subject allocation rate between the exposed and control groups was 1:1. This indicated the need for an additional 300 mothers and 300 children to constitute the nonexposed control groups. Hence, the overall sample size of the PROUDEST was set to 1200 participants (600 mother-child dyads consisting of 300 SARS-CoV-2–exposed mother-child dyads and 300 control dyads).

To promote participant retention and completed follow-ups at pregnancy and pediatric outpatient clinics, we will actively search for patients via phone and email.

### Procedures

A host of clinical, psychological, neurodevelopmental, biochemical, histological, and imaging assessments will be conducted in accordance with the PROUDEST protocol (Figure 2).

**Figure 2 figure2:**
[figure not shown]
PROUDEST study design. CNS: central nervous system; MRI: magnetic resonance imaging; PROUDEST: Pregnancy Outcomes and Child Development Effects of SARS-CoV-2 Infection Study.

Prenatal data from both the pregnant women and their fetuses will be gathered during the follow-up at the Pregnancy Outpatient Clinic of the University Hospital of Brasilia. These data will consist of the medical and sociodemographic data of the mothers; gestational age; symptoms, interventions, and outcomes related to COVID-19 (for SARS-CoV-2–exposed participants); congenital infection screening results; hypertensive disorders and other pregnancy-specific morbidities; general health assessments; general physical examinations; routine clinical biochemistry tests; and ultrasound scans. These scans will be performed between gestational weeks 11-13 and gestational day 6, from gestational week 22 to gestational week 24, and on a monthly basis in the third trimester of pregnancy to assess fetal growth and morphology, placental morphology, amniotic fluid volume, and dopplerfluxometry results. Maternal blood will be collected at the first prenatal consultation, regardless of gestational age. Antenatal consultations will occur monthly up to week 34, every 2 weeks between weeks 34 and 36, and then weekly up to delivery. During pregnancy, psychological risk assessments and mental health screens will be performed with the Beck Depression Inventory during the first prenatal consultation. [40]. Individual psychological care will be provided to pregnant women who have a Beck Depression Inventory score of >12. Mothers will also be physically and psychologically evaluated between days 7 and 21 postpartum during the PREGNANT substudy and after the BORN substudy.

At childbirth, assessments will be conducted to identify the occurrence of dysfunctional labor and the premature rupture of membranes, the type of birth, and delivery outcomes. We will also conduct physical examinations and classifications of the newborns and anthropometry. The early initiation of breastfeeding, the need for neonatal intensive care, and the type of interventions will also be identified. Maternal blood, CSF from women undergoing spinal anesthesia for a cesarean section, and umbilical cord blood samples will be collected.

CSF will be collected immediately before the infusion of the medicine for spinal anesthesia, which will be injected via a sterile syringe at an average dosage of 0.5 ml. CSF will be collected in a 4-mL cryotube. Blood samples from mothers and the umbilical cord will be collected in a heparinized tube and centrifuged immediately, and the plasma will be stored in 4-mL sealed cryotubes. CSF and blood samples will be subsequently stored at −80 °C for later analysis. The assessment of blood cell counts, inflammation markers (C-reactive protein and procalcitonin), biochemistry (alanine aminotransferase, aspartate aminotransferase, ferritin, alkaline phosphatase, and lactic dehydrogenase) and SARS-CoV-2 tests (RT-PCR and IgM and IgG antibody tests) will be carried out.

Circulating cytokine levels will be evaluated with the Luminex Bio-Plex Pro Human Cytokine 27 platform (Bio-Rad Laboratories). The cytokine profile assessment will analyze chemokines (CXC motif chemokine ligand [CXCL] 8, CC motif chemokine ligand [CCL] 11, CCL3, CCL4, CCL2, CCL5, and CXCL10), proinflammatory cytokines (interleukin [IL]-1β, IL-6, tumor necrosis factor, IL-12p70, interferon γ, IL-17A, and IL-15), regulatory cytokines (IL-1Ra, IL-4, IL-5, IL-9, IL-10, and IL-13), and cell growth factors (IL-2, IL-7, basic fibroblast growth factor, platelet-derived growth factor, vascular endothelial growth factor, granulocyte colony-stimulating factor, and granulocyte-macrophage colony-stimulating factor). All procedures will be performed according to the manufacturer's recommendations.

Analyses will be performed at the clinical biochemistry laboratories of the hospitals where delivery occurred (blood cell count, C-reactive protein, procalcitonin, and routine biochemistry assessments), the Central Laboratory of the Federal District Department of Health (Laboratório Central de Saúde Pública; SARS-CoV-2 tests), and the University of Brasilia laboratory (cytokine profile assessments).

The placenta will be subjected to fresh histopathological analyses for assessing possible morphological and histological changes that may be associated with SARS-CoV2 infection. Histopathological analysis will be conducted according to the Amsterdam protocol [41].

Peripheral blood and CSF samples from the newborns will only be collected if there is clinical need; this will not be done per the routine research protocol. If such specimens are made available, they will also be subjected to the aforementioned analyses.

All newborns will undergo neonatal screening tests in accordance with the recommendations of the Ministry of Health of Brazil. Five drops of blood will be collected on filter paper for the national neonatal screening program. This blood sample will be collected after 48 hours of life and will be used to screen for the following diseases: phenylketonuria, congenital hypothyroidism, biotinidase deficiency, cystic fibrosis, and congenital adrenal hyperplasia. After 24 hours of life and before discharge, a pulse oximetry test will be performed. Oxygen saturation in the right upper limb and one of the lower limbs will be measured. The pulse oximetry test will be considered normal if oxygen saturation is ≥95% and the difference between the limbs is not ≥3%. Hearing screening will be performed between 36 and 48 hours of life by analyzing otoacoustic emissions.

After hospital discharge, all neonates will be followed up at the Pediatric Outpatient Clinic of the University Hospital of Brasilia. Child growth and neurodevelopment will be assessed at all visits. The first visit will be scheduled to occur on day 15 postpartum. Afterward, visits will be conducted monthly during the first 6 months of life. Thereafter, visits will be scheduled every 3 months until the children reach 12 months of age and every 6 months until the children reach 5 years of age. Nonscheduled visits may occur due to urgent clinical needs. The outpatient clinic staff (a multidisciplinary team) will be composed of pediatricians, psychologists, occupational therapists, speech therapists, physiotherapists, and nurses. The psychological effects of SARS-CoV-2 infection on mothers will be assessed with the Edinburgh Postnatal Depression Scale [42]. This assessment will occur more than once until their children reach 6 months of age. Breastfeeding and weaning patterns, dietary habits, nutritional status, and vaccinal status will be assessed throughout the study.

The assessment of children’s neurodevelopment will be carried out until they reach the 60th month of life. This assessment will analyze cognitive, motor, socioemotional, and language-related aspects and adaptive behavior. The evaluation will be conducted by using the Bayley III Child Development Scale (ie, the version validated for Brazilian infants) [43]. From the age of 2.5 years onward, aspects related to intellectual performance will also be assessed by using the Wechsler Preschool and Primary Intelligence Scale, third edition at 6-month intervals [44].

Central nervous system imaging assessments will be carried out via transcranial ultrasound doppler scans, which will be performed between the 15th and 90th day of the child's life. A brain magnetic resonance imaging scan will be performed if altered cephalic perimeter measures, neurological development delays, or abnormal ultrasound doppler scan findings are identified.

Blood will be collected from SARS-CoV-2–exposed children aged 12 and 24 months to assess their metabolic profiles, which will be used to identify the long-term effects of SARS-CoV-2 infection on systemic metabolism that are potentially driven by past viral exposure and associated inflammatory responses. The examination will consist of assessments for energy metabolism markers (serum lipids, glucose, and insulin), thyroid function markers (thyroid-stimulating hormone and free thyroxine), bone metabolism markers (parathyroid hormone, calcium, phosphate, alkaline phosphatase, and 25-hydroxyvitamin D), adrenal tonus indicators (adrenocorticotropic hormone and basal cortisol), and renal function markers (blood urea nitrogen, creatinine, and urine analysis results).

All newborns will undergo extended hearing screening. Evoked otoacoustic emission and brainstem auditory-evoked potential tests will be performed during the child’s first year of life.

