**Figure 1 figure1:**
[figure not shown]
Pregnancy Outcomes and Child Development Effects of SARS-CoV-2 Infection Study follow-up flowchart.

The PREGNANT substudy will follow—until day 21 postpartum—pregnant women who are exposed to SARS-CoV-2 at any phase of gestation and compare them to a control group consisting of nonexposed pregnant women. The BORN substudy will follow the children of the women included in the preceding (PREGNANT) branch. These children will be allocated into two comparison groups (exposed and nonexposed) according to their mothers’ in-pregnancy exposure status and will be followed up by a multidisciplinary team of health professionals from birth up to the age of 5 years. This team will conduct regular consultations every month up until the children reach 6 months of age, every 3 months up until the children reach 2 years of age, and every 6 months up until the children reach 5 years of age. Mothers and children may attend nonscheduled visits, as needed, for clinical reasons as well as specific appointments for conducting the procedures and tests described in this protocol.

The PROUDEST will be conducted from July 2020 to December 2026 in Brasília, Brazil. The recruitment of pregnant and newborn dyads will be carried out by using data from the Epidemiological Surveillance Center of the Federal District. These mother-fetus dyads will be followed up to childbirth (and puerperium in the case of mothers) until December 2021, which is when the last included dyads are expected to undergo childbirth in two different hospitals—the University Hospital of Brasília and Asa Norte Regional Hospital (the reference public medical center for COVID-19 in the Federal District in Brazil). Both hospitals are located in central urban areas and are included in the Brazilian public health system (Sistema Único de Saúde), which primarily serves the low-income population. Thus, the results of the PREGNANT substudy will be published as soon as the analyses are completed. The children will be followed from childbirth up to December 2026, which is when the last admitted neonate will turn 5 years old. As the BORN substudy is lengthy, partial results may be disclosed during the course of the study, but the final data set will be made available in the second half of 2026.

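### No masking of placental readers or developmental examiners to maternal exposure is described, and features the article does state would reveal exposure in the child clinic

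*Protocol article*

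**What the plan says.** All references are to the protocol article.

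- **Placenta (Procedures).** The stated purpose is: "The placenta will be subjected to fresh histopathological analyses for assessing possible morphological and histological changes that may be associated with SARS-CoV2 infection". Readings follow the Amsterdam protocol. The section names laboratories for biochemistry, SARS-CoV-2 tests and cytokines, but no placental reader or laboratory.
- **Child development (Procedures).** "The evaluation will be conducted by using the Bayley III Child Development Scale", with Wechsler testing added from 2.5 years. No examiner is named.
- **Who sees the children.** Under Study Design, children are grouped by maternal exposure and "will be followed up by a multidisciplinary team of health professionals from birth up to the age of 5 years". Under Procedures, "The outpatient clinic staff (a multidisciplinary team) will be composed of pediatricians, psychologists, occupational therapists, speech therapists, physiotherapists, and nurses". The Discussion adds that this team's care is guaranteed to every BORN child throughout the study.
- **Exposed-only procedures.** COVID-19 symptoms, interventions and outcomes are recorded for exposed mothers. In the child clinic, "Blood will be collected from SARS-CoV-2–exposed children aged 12 and 24 months to assess their metabolic profiles".
- **MRI.** "A brain magnetic resonance imaging scan will be performed if altered cephalic perimeter measures, neurological development delays, or abnormal ultrasound doppler scan findings are identified".
- **Protection against bias.** Statistical Analysis and the limitations in the Discussion rely on adjusting for differences found between the groups. Neither mentions what assessors know.

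**The concern.** Bayley III and Wechsler items are given and scored by an examiner, and placental lesions are recognised and graded by a reader. Both leave some room for expectation. If the assessor knows which mothers were infected, the same child or placenta may be rated differently according to exposure. The difference then sits in the measured outcome itself and looks like an effect of exposure, or hides one.

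The planned adjustment acts on background features such as maternal age or comorbidity. It cannot correct an outcome recorded differently in the two groups, and an analyst cannot repair it afterwards. Aim 9, the effect of exposure on children's development, depends most directly on these ratings. A judged delay is also one of the routes to a brain MRI, so differential rating could lead to differential scanning.

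**Working it through.** **Step 1. Is masking described?** No. The article says neither that assessors are masked nor that they know exposure status.

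**Step 2. Would exposure be visible if the study ran as described?**

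| Setting | Features stated | Reading |
|---|---|---|
| Child clinic | One team for both groups, which also gives care; maternal COVID-19 data for the exposed; blood draws at 12 and 24 months described for exposed children only | Exposure probably visible |
| Placenta | Exposure rests on a positive test in pregnancy; nonexposure is confirmed by serology 14–21 days postpartum; no reader named | A positive test can be known before the reading, control status is not yet final; an inference only |

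The blood draws are a cue from 12 months onward. They do not explain visibility at earlier visits, where shared care and the maternal history are the route.

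**Step 3. How large a rating gap would matter?** The article gives no figure here, so this is an illustration.

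Inputs: 300 children per group and 20% dropout (Sample Size Calculation); P<.05 (Statistical Analysis), taken as two-sided; score SD of 15 (assumed).

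- Children per group: 300 × 0.8 = 240.
- Standard error of the difference: 15 × √(2/240) = 1.37 points.
- Gap that puts the expected statistic at the threshold: 1.96 × 1.37 = 2.68 points, and 2.68/15 = 0.18 SD.
- Chance of P<.05 with no true effect, Φ(gap/SE − 1.96):

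| Rating gap (points) | 240 per group |
|---|---|
| 1 | 11% |
| 2 | 31% |
| 3 | 59% |
| 4 | 83% |

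**Step 4. The same for a yes/no reading**, such as a placental lesion, with 300 per group. Let p be the true rate in both groups and f the share of truly normal exposed subjects rated abnormal. The apparent exposed rate is p + f(1 − p). For p = 10% and f = 5% it is 0.10 + 0.05 × 0.90 = 0.145, an apparent relative risk of 1.45. Both p and f are assumed.

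| True rate p | f = 2% | f = 5% | f = 10% |
|---|---|---|---|
| 5% | 16% | 60% | 98% |
| 10% | 11% | 39% | 88% |
| 20% | 7% | 22% | 63% |

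Cells give the chance of P<.05 with no true effect. The result depends almost wholly on f, about which the article says nothing.

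**The case against.** The strongest reply is that this argues from silence in a condensed article. Masking of assessors is an operational detail that the full protocol may hold. Much of this stands. A reader might infer that placentas and children are judged by staff who know which dyads were exposed, and the article does not say so. The sentence on histology gives the purpose of the reading, not what the reader knows. Nor does the article say that the tester is the treating clinician. What remains does not rest on silence alone: the stated features of the child clinic would reveal exposure unless something were done to hide it.

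Other objections also limit the point:

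- **Standard instruments.** Bayley III, the Wechsler scale and the Amsterdam protocol narrow the room for expectation. They do not close it, and they do not conceal status.
- **Aim 5.** It is tempting to say that this aim rests on an exposed-control contrast in placental readings. As worded it states none. Group comparison enters only through the general Statistical Analysis text, and aim 6 relates the histologic markers to outcomes.
- **Direction.** A reader might assume that the bias must run toward harm. That is unproven: lenient scoring of exposed children would hide harm.
- **MRI.** The rule is worded alike for all children, and two of its three triggers are not a judged delay. A lower threshold in exposed children is possible but is not stated. No aim names MRI lesions as an outcome, and no analysis restricted to scanned children is planned.
- **Size.** Nothing in the article suggests that a gap of 2.7 points would occur.

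**Conclusion.** The concern holds in a limited form. The article describes no masking for outcomes that depend on judgement. For developmental testing, its own procedures would probably make exposure visible. For placental histology the risk is a weaker inference, because no reader is named. If rating differs by exposure, the comparison is biased in a direction that cannot be known beforehand, and the adjustment that the article relies on cannot remove it.

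The figures show how sensitive the comparison is, not how much bias to expect. With an assumed SD of 15, 240 children per group and a two-sided 5% test, a gap of about 2.7 points (0.18 SD) is enough to put the expected statistic at the threshold. The document does not support saying that assessors do know exposure, or that an effect found will be due to expectation. A change is still worth making, because differential rating cannot be corrected once the data are recorded.

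**What to change.** 1. **Placentas.** Send them to pathology under the study code, with gestational age but without SARS-CoV-2 status. Release status only after the Amsterdam reading is locked.
2. **Developmental tests.** Have the existing psychologist or therapist who gives the Bayley and Wechsler tests work from a REDCap view that hides maternal exposure. The treating pediatrician keeps the history.
3. **MRI.** Leave the criteria to the investigators and apply them alike in both groups. If MRI findings are compared between groups, report them over all children followed and give the scan rate per group.
4. **Reporting.** If masking is already in the full protocol, say so in a sentence. In either case, list incomplete masking of child examiners as a limitation.

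The cost is coded request forms, a REDCap access setting and some protocol wording, with existing staff. Masking of placental readers can be nearly complete. Masking of child examiners cannot, since some mothers will disclose their history. The change was still timely at the January 2021 status: recruitment had begun only in July 2020, so all Wechsler testing, which starts at 2.5 years, and most Bayley testing lay ahead. Some placentas may already have been read, and the report should say whether those readings were masked.

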### Statistical Analysis

All data will be stored in REDCap (Research Electronic Data Capture; Vanderbilt University), which is a tool for building and managing web-based surveys and databases. All variables will be summarized via standard descriptive techniques according to their type and distribution. For the bivariate analysis, differences in categorical variables between the exposed and unexposed groups will be verified with the Chi-square test or Fisher exact test, whereas differences in continuous variables between the groups will be assessed with the Student *t* test or the Mann-Whitney U test.

For dichotomous outcomes, binomial regression models, which will be adjusted based on the unbalanced and relevant background features of the comparison groups, will be used to estimate the relative risks between the exposed and nonexposed groups. Partial correlation and general linear models will be used to assess the associations between continuous outcome variables and covariates; adjustments for imbalances will be made as appropriate. A *P* value of <.05 will be considered significant. The control group will be composed of nonexposed mother-child dyads that meet the inclusion criteria. However, those with positive serology tests (IgG and IgM tests conducted at 14-21 days postpartum) will not be included in the control group. The groups will not be matched or paired based on age or other variables. However, any differences between the groups will be adjusted later via statistical means.

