### Objective

Our specific aims are (1) to study the effects of COVID-19 on maternal and obstetric morbidity and mortality, including those of indicators such as preeclampsia, abortion, fetal malformation, fetal growth, and premature birth; (2) to investigate the presence of SARS-CoV-2 and anti–SARS-CoV-2 antibodies in the cerebrospinal fluid (CSF) of women with symptomatic COVID-19 undergoing spinal anesthesia for a cesarean section; (3) to determine the serum proinflammatory and regulatory cytokine profiles of pregnant women with symptomatic COVID-19; (4) to determine the CSF proinflammatory and regulatory cytokine profiles of pregnant women with symptomatic COVID-19 undergoing spinal anesthesia for a cesarean section; (5) to study the histopathological markers of inflammatory and thrombotic phenomena in the placenta; (6) to study the correlations between the aforementioned serum and histologic biomarkers of COVID-19 and the outcomes of pregnancy, delivery, puerperium, and childbirth as well as the correlations between biomarkers and short- and long-term health outcomes during infancy; (7) to study the association between the use of maternal pharmacological therapy for treating COVID-19 and offsprings’ health outcomes; (8) to evaluate the effects of COVID-19 exposure during different stages of pregnancy on fetal, neonatal, and infantile morbidity and mortality; and (9) to evaluate the effects of in-pregnancy COVID-19 exposure on children’s somatic and neurological development and energy metabolism from birth up to 5 years of age.

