Pregnant women included in the study must be aged >18 years. COVID-19 exposure will be defined as a first-time RT-PCR test, serology test, or rapid test that returns positive results during pregnancy and is confirmed by a second test. Nonexposure to COVID-19 will be defined as asymptomatic pregnant women with negative serology tests (immunoglobulin G [IgG] and immunoglobulin M [IgM] tests), which will be conducted at 14-21 days postpartum.

Pregnant women with preexisting chronic diseases (except diabetes and hypertension); those taking continuous medications; those who consume tobacco, alcohol, or other drugs; and those with other suspected or confirmed congenital infections will be excluded.

Neonates whose mothers qualified for inclusion in the PREGNANT substudy (had these women been screened) may also be admitted to the BORN substudy, even if their mothers did not participate in the preceding branch.

Children initially assigned to the control (nonexposed) group who later become infected with SARS-CoV-2 (as confirmed via laboratory tests) during follow-up will be excluded from all analyses (from the time of SARS-CoV-2 infection diagnosis onward). However, they will continue to receive assistance under the same standards until the end of the study.

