The study does have several limitations. Its observational nature limits inferences for causal associations to some extent. However, the cohort study design is the closest observational equivalent to a clinical trial in terms of analytical power, and the objective of the PROUDEST does not ethically allow for interventional experiments because such experiments would imply that pregnant woman will be randomized based on SARS-CoV-2 infection. Moreover, the purpose of the study is to characterize the clinical and pathophysiological phenomena associated with SARS-CoV-2 infection during pregnancy and infancy, not to test the efficacy of any intervention. Thus, we believe that a cohort study is the best possible study design for addressing our objectives. The lack of random allocation for comparison groups will be partially compensated by statistically adjusting for the observed imbalances. Vaccination for SARS-CoV-2 will not be an exclusion criterion because due to the vaccine’s limited accessibility and availability, there are no feasible methods for estimating the proportion of pregnant women that will receive the vaccine. However, the effects of SARS-CoV-2 vaccination can be adjusted and analyzed in small control groups that have either received or not received the vaccine.

The protracted follow-up in the BORN substudy is expected to result in the dropout of several participants. We set a sample size for the study after taking into consideration a 20% loss to follow-up rate. This might ensure that a sizable number of children are available for the final assessment when they reach age of 5 years. However, we cannot avoid survival bias in the long-term data. Nevertheless, given that the continuity of multidisciplinary assistance will be guaranteed for all children in the BORN branch throughout the study period regardless of their withdrawal from the analysis or (temporary) losses to follow-up, we expect that children experiencing health problems associated with in-pregnancy COVID-19 exposure will be less likely to drop out than those who are in perfect health. Therefore, we do expect to have a sufficient number of children in the long run for identifying developmental abnormalities (should they exist), even after some amount of dropout.

Several routine pediatric consultations will be emphasized in the study, such as checking the kind of alimentation that a child is receiving (human milk or formula milk) and promoting the practice of breastfeeding.

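### BORN outcomes counted as ever/never over follow-up get a binomial model without follow-up time, although control children alone leave the analysis at their own infection

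*Protocol article*

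**What the plan says.** In the protocol article, the Statistical Analysis section names a single approach for yes/no outcomes: "For dichotomous outcomes, binomial regression models, which will be adjusted based on the unbalanced and relevant background features of the comparison groups", which "will be used to estimate the relative risks between the exposed and nonexposed groups". It does not separate outcomes known at delivery from outcomes that accrue over years, and it names no person-time or time-to-event method.

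Three other places bear on this:

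- **Study Design, follow-up.** Children are followed "from birth up to the age of 5 years".
- **Study Design, exclusions.** "Children initially assigned to the control (nonexposed) group who later become infected with SARS-CoV-2", confirmed by laboratory test, "will be excluded from all analyses (from the time of SARS-CoV-2 infection diagnosis onward"). Data before the diagnosis stay in. No matching rule is given for exposed children who are themselves infected after birth.
- **Discussion, limitations.** "We set a sample size for the study after taking into consideration a 20% loss to follow-up rate". The same paragraph expects children with exposure-related health problems to drop out less often than healthy ones.

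Aim 8 in the Objective section is "to evaluate the effects of COVID-19 exposure during different stages of pregnancy on fetal, neonatal, and infantile morbidity and mortality". Death and a first morbidity event build up over follow-up.

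**The concern.** A plain binomial model of ever versus never treats each child as observed for the same length of time. The exclusion rule makes that untrue in one group only: a control child diagnosed at 18 months contributes 18 months, while an exposed child diagnosed at the same age goes on contributing. The control group therefore has less time in which events can be seen.

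The analyst must then code the children who left early without an event. If they count as event-free, control risk is understated and the relative risk rises. If they are dropped while children whose event came before leaving are kept, control risk is overstated and the relative risk falls. The same data with no true effect could thus be read as harm or as protection. The exposed-versus-nonexposed comparison of child outcomes is the purpose of BORN, so this matters for any such outcome.

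**Working it through.** The documents give no relative risk, event rate or child infection rate for this point, so there is no stated figure to reproduce. The check asks what relative risk is expected when exposure has no effect.

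**Inputs from the protocol article:** 300 children per group (Sample Size Calculation); 5 years of follow-up; 20% loss, taken as equal in both groups and spread evenly; significance level 0.05, taken as two-sided.

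**Assumptions:** event rate h = 0.04 per year in both groups, a true 5-year risk of 1 − exp(−0.20) = 18.1%; extra removal of controls at rate c = 0.02 to 0.20 per year; constant rates; leaving independent of outcome.

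**Formulas.** Dropout rate d = −ln(0.8)/5 = 0.0446 per year. With total rate t = h + d + c (c = 0 in the exposed):

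- share with an observed event: A = (h/t)(1 − exp(−5t))
- share still followed and event-free at 5 years: S = exp(−5t)
- coding 1, early leavers counted as event-free: risk = A
- coding 2, early leavers without an event dropped: risk = A/(A + S)

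**Worked case, c = 0.10:**

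- Exposed: t = 0.0846, S = 0.655, A = (0.04/0.0846)(0.345) = 0.163.
- Control: t = 0.1846, S = 0.397, A = (0.04/0.1846)(0.603) = 0.131.
- Coding 1: 16.3% against 13.1%, relative risk 1.25.
- Coding 2: 0.163/0.818 = 19.9% against 0.131/0.528 = 24.7%, relative risk 0.81.

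| Control removal per year (assumed) | Null RR, coding 1 | Null RR, coding 2 | Rejection at nominal 5% (coding 1 / 2) |
|---|---|---|---|
| 0 | 1.00 | 1.00 | 5% / 5% |
| 2% | 1.05 | 0.96 | 6% / 6% |
| 5% | 1.12 | 0.90 | 9% / 9% |
| 10% | 1.25 | 0.81 | 20% / 21% |
| 20% | 1.53 | 0.65 | 52% / 58% |

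Rejection is from a two-proportion test starting from 300 per group. The coding 1 ratio hardly depends on the event rate: at 10% removal it is 1.25 for 2% events per year and 1.24 for 8%. In the first row the ratio is right, but each risk is off by about a tenth of its value (16.3% or 19.9% against 18.1%).

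**Where the bias does not arise.** Take only children followed to age 5, whatever their event status, for a non-fatal outcome. If leaving is independent of outcome, the expected risk is 18.1% in both groups at every removal rate, which simulation confirmed. The cost is precision: at c = 0.10, 300 × exp(−5 × 0.1446) = 146 controls remain, against 300 × 0.8 = 240 exposed.

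**What the alternative does.** Expected events divided by expected person-time is A / [(1 − exp(−5t))/t] = h in both groups, so the null rate ratio is 1. Simulation agreed (2,000 runs per setting, 20% equal dropout, true 5-year risks of 10% to 30%, 2% to 20% of controls infected per year): rate ratios were 0.99 to 1.02, with rejection of 4.6% to 5.5%.

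**The case against.** The strongest reply is that the biased analysis is not written down. The article does not list which yes/no child outcomes are cumulative. Aim 8 sets no 5-year first-event definition, and its comparisons between stages of pregnancy lie within the exposed group, where the control-only rule does not act. Aim 9, which does run to 5 years, covers growth, development and metabolism, and many of those measures are continuous. Outcome windows and denominators are commonly left to an analysis plan. A binomial family can also be made to carry time, for example with one record per child and period.

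Much of this stands, and it limits the point to outcomes counted as ever/never over follow-up and compared between exposed and nonexposed children. It does not remove the point. The article positively chooses a relative-risk model for all yes/no outcomes, adjusted for background features only, and pairs it with a rule that shortens follow-up in one group. Mortality is named in the aims, and restricting to children followed to a given age does not work for death.

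A reader might infer that the BORN relative risks are wrong in general, or that a binomial model can never be valid here. The documents do not support that. Delivery outcomes are untouched, and non-fatal fixed-age assessments are not biased in this way if leaving is unrelated to outcome. With equal dropout and no control removal the null ratio is 1.00, so the between-group bias comes from the model and the one-sided rule together.

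**Conclusion.** The point holds for ever/never BORN outcomes over follow-up, such as death or a first morbidity event. There the stated model and the stated removal rule do not fit together, and the null relative risk moves away from 1 in a direction set by how early leavers are coded.

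The size is uncertain because the documents give no infection rate in children. At 2% per year the effect is minor. At 10% per year it gives a false relative risk of about 1.25 or 0.81 and roughly four times the nominal false-positive rate; at 20% it is larger still. These figures rest on constant rates, a 4% per year event rate, equal 20% dropout, and leaving that is independent of outcome. The health-related dropout foreseen in the Discussion would break the last assumption and is not included in them.

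**What to change.** For BORN outcomes that accumulate over follow-up, replace the binomial model by time-to-first-event analysis. Censor children at their last analysed visit, treat death as a competing event for non-fatal outcomes, and report adjusted risk ratios from the cumulative incidence at stated ages. If Poisson regression with log follow-up time is used instead, report the results as rate ratios, since they are not risks by a given age. Keep binomial models for delivery outcomes and fixed-age assessments.

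State that the method assumes leaving is independent of outcome, and add a sensitivity analysis, for example inverse-probability-of-censoring weights or the same censoring at infection applied to both groups. This is needed because the method alone cures neither the one-sided removal rule nor the health-related dropout.

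The cost is a paragraph of text and somewhat more analysis work. Visit, event and infection dates must be recorded; infection dates are needed in exposed children too if the symmetric censoring analysis is chosen. The article schedules analysis to begin only once data collection is complete, so the change can be made beforehand.
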